### 3. STUDY DESIGN

This is a three arm open-label prospective randomized controlled trial. (n=150) The trial is designed to compare the efficacy of treatment with Peg-IFN and ADF or Peg-IFN and TDF versus no treatment for clearance of the HBsAg in chronic hepatitis B patients with low viral load.

Patients will be enrolled into the study after assessment of eligibility. Group 1 will consist of patients treated with Peg-IFN 180µg once weekly and ADF 10mg once daily (standard doses), group 2 will consist of patients treated with Peg-IFN 180µg once weekly and TDF 300mg (equivalent to 245 mg tenofovir disoproxil) once daily (standard doses) and group 3 will consist of untreated patients as negative controls.

The trial consists of a screening period of approximately 4 weeks, a 48 week treatment period, a 24 week follow-up period and a long term follow up period of 5 year. A schematic overview of the study design is presented in table 1 and 2 (see appendix).

150 patients will be randomized in a 50:50:50 ratio to one of the treatment groups.

Randomization will be stratified to genotype A to optimize balance between treatment groups. All patients will receive medication for the period of 48 weeks. For enrolment into the study a liver biopsy at time of enrolment is compulsory for patients selected in the treatment groups. For enrolment of patients that are selected in the non-treatment group a liverbiopsy is optional but not compulsory for participation. In patients selected in the treatment group a second liver biopsy at week 48 is recommended for evaluation of therapeutic responses and to guide any further possible therapy. Due to the burden of undergoing a liver biopsy, the second liver biopsy is not compulsory to take part into the study. Patients that are selected in the non treatment group will not undergo a biopsy at week 48. Patients will be clinically monitored intensively according to the assessment schedule (table 1). In the long term follow up period patients will be clinically monitored each year.

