### Study design:

This is a three arm open-label prospective randomized controlled trial. 150 patients will be enrolled into the study after assessment of eligibility. All patients must have documented HBsAg positivity for longer than 6 months, HBeAg negativity, anti-HBe positivity, HBV DNA < 20,000 IU/mL and ALT < 5 \* upper limit of normal. Patients with a Child Pugh class B or C will be excluded. Group 1 will consist of patients treated with Peg-IFN and adefovir, group 2 will consist of patients treated with Peg-IFN and tenofovir and group 3 will consist of untreated controls. Patients in group 1 and 2 will receive medication for the period of one year. For enrolment into the study a liverbiopsy at time of enrolment is compulsory and is advisable at end of treatment (week 48).

**Study population:** The study population will consist of 150 patients chronically infected with hepatitis B virus with low viral load and HBeAg negativity.

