16. History or other evidence of chronic pulmonary and cardiac disease associated with functional limitation. Severe cardiac disease (e.g., NYHA Functional Class III or IV, myocardial infarction within 6 months, ventricular tachyarrhythmias requiring ongoing treatment, unstable angina or other significant cardiovascular diseases).
17. History of a severe seizure disorder or current anticonvulsant use and clinically unstable disease.
18. Evidence of an active or suspected cancer or a history of malignancy where the risk of recurrence is  $\geq 20\%$  within 5 years. Patients with a lesion suspicious of hepatic malignancy on a screening imaging study will only be eligible if the likelihood of carcinoma is  $\leq 10\%$  following an appropriate evaluation.
19. Major organ transplantation. (patients with skin, cornea or bone transplantation are allowed to be included into the study)

20. Thyroid disease with thyroid function poorly controlled on prescribed medications. Patients with elevated thyroid stimulating hormone or T4 concentrations, with elevation of antibodies to thyroid peroxidase and any clinical manifestations of thyroid disease that are not stable on prescribed medication are excluded. Stable patients can be included.
21. History or other evidence of severe retinopathy (e.g. CMV retinitis, macula degeneration) or clinically relevant ophthalmological disorder due to diabetes mellitus or hypertension.
22. Inability or unwillingness to provide informed consent or abide by the requirements of the study.
23. History or other evidence of severe illness or any other conditions which would make the patient, in the opinion of the investigator, unsuitable for the study.
24. Patients with a value of alfa-fetoprotein >100 ng/mL are excluded, unless stability (less than 10% increase) has been documented over at least the previous 3 months.
25. Evidence of current hard drug(s) (i.e. cannabis products are allowed) and/or alcohol abuse (20g/day for women and 30g/day for men).
26. Patients included in another trial or having been given investigational drugs within 12 weeks prior to screening.

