### **7.2. Randomisation, blinding and treatment allocation**

Patients will be randomized unblinded to one of the 3 groups. A stratification for hepatitis B genotype A will be performed.

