## Schedule of Assessments

Table 1. Schedule of Assesments

| Assessment/ Procedure                                   | Screening
(weeks) | Study treatment Period Peg-INF and ADF, Peg-IFN and tenofovir or no treatment
(weeks) |       |   |   |   |   |   |    |    |    |    |    |    |    | Follow-up
(weeks) |   |   |    |    |    |    |
|---------------------------------------------------------|----------------------|------------------------------------------------------------------------------------------|-------|---|---|---|---|---|----|----|----|----|----|----|----|----------------------|---|---|----|----|----|----|
|                                                         |                      | B                                                                                        | Day 3 | 1 | 2 | 4 | 6 | 8 | 12 | 18 | 24 | 30 | 36 | 42 | 48 | 2                    | 4 | 8 | 12 | 16 | 20 | 24 |
| Study weeks                                             | -4 to 0              |                                                                                          |       |   |   |   |   |   |    |    |    |    |    |    |    |                      |   |   |    |    |    |    |
| Informed consent, medical history                       | X                    |                                                                                          |       |   |   |   |   |   |    |    |    |    |    |    |    |                      |   |   |    |    |    |    |
| Physical examination                                    | X                    | X                                                                                        |       | X | X | X |   | X | X  |    | X  |    | X  |    | X  |                      | X |   | X  |    |    | X  |
| Liver biopsy (preceding 12 months)                      | X                    |                                                                                          |       |   |   |   |   |   |    |    |    |    |    |    | X  |                      |   |   |    |    |    |    |
| Urine or serum pregnancy test a              |                      | X                                                                                        |       |   |   | X |   | X | X  | X  | X  | X  | X  | X  | X  |                      | X | X | X  | X  | X  | X  |

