## HBsAg loss during treatment with Peg-IFN combined with ADV or TDF

|                                         |   |   |   |   |   |   |   |   |   |   |   |   |   |   |   |   |   |   |   |   |   |   |
|-----------------------------------------|---|---|---|---|---|---|---|---|---|---|---|---|---|---|---|---|---|---|---|---|---|---|
| PBMC's (frozen for central processing)  | X | X | X | X |   | X |   | X | X |   | X |   | X |   | X | X |   |   |   |   |   | X |
| PAXgene™ DNA (j) (human genomics)       |   | X |   |   |   |   |   |   |   |   |   |   |   |   |   |   |   |   |   |   |   |   |
| PAXgene™ RNA (k) (human genomics)       |   | X |   |   |   | X |   |   | X |   |   |   |   |   | X | X |   |   |   |   |   | X |
| Plasma tube (proteomics profiling ) (l) |   | X |   |   |   | X |   |   | X |   |   |   |   |   | X | X |   |   |   |   |   | X |
| Adverse events                          |   | X | X | X | X | X | X | X | X | X | X | X | X | X | X | X | X | X | X | X | X | X |
| Quality of life (m)                     |   | X |   |   |   |   |   |   | X |   |   |   |   |   | X |   | X |   |   |   |   | X |
|                                         |   |   |   |   |   |   |   |   |   |   |   |   |   |   |   |   |   |   |   |   |   |   |

Chemistry 1 : ASAT, ALAT,

Chemistry 2: sodium, chloride, potassium, bilirubin, creatinine, urea, prothrombin time, APTT, antitrombine III, alkaline phosphatase, calcium, phosphorus, total protein, albumin, uric acid, TSH, free T4 and glucose.

Chemistry 3: cholesterol, triglycerides, sober glucose

B: baseline

- (a) For females of child bearing potential only, a pregnancy test will be performed within 24 hours prior to first dose. A pregnancy test must be done at any time a secondary amenorrhea of more than 1 week occurs.
- (b) Only for patients with pre-existing pulmonary disease (Not necessary if (1) a chest X-ray available to the investigator has been obtained within the past 12 months and (2) the patient's pulmonary disease has been clinically stable)
- (c) Patients with cirrhosis or marked fibrosis on liver biopsy or raised AFP need to have a liver imaging study during the screening period to rule out hepatic neoplasia.
- (d) For anyone with preexisting cardiac disease.

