| Liver Biopsy (a)              | Performed at start of the study and repeated after 48 weeks.                                                                                                                                                                                                                                                                                                  |
| Fibroscan (b)                 | Performed at start of the study and repeated after 48 weeks.                                                                                                                                                                                                                                                                                                  |
| Liver Imaging (ultrasound)               | Performed at screening or start of the study, repeated after 48 weeks and on indication.                                                                                                                                                                                                                                                                      |
| Liver Imaging (CT or MRI)                | Only for patients suspected to have hepatic neoplasia.                                                                                                                                                                                                                                                                                                        |
| HCG Pregnancy Test                       | For women of childbearing potential a negative urine (or serum) HCG test needs to be documented within 24 hours prior to the first dose.                                                                                                                                                                                                                      |

(a) When a participant has objections against a second liver biopsy at week 48 ,he or she can refuse it. The participant will than not be excluded from the study.

(b) A fibroscan measures the liver stiffness, expressed in kilopascals (kPA)

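### Section 3 makes a baseline biopsy an entry condition only for patients in the treatment groups, so entry depends on the open-label allocation, and other parts of the protocol contradict the rule

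*Protocol*

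**What the plan says.** Section 3 of the Protocol sets two rules. For the active arms: "For enrolment into the study a liver biopsy at time of enrolment is compulsory for patients selected in the treatment groups". For controls: "For enrolment of patients that are selected in the non-treatment group a liverbiopsy is optional but not compulsory for participation". The same section assigns 150 patients to the three groups by 50:50:50 randomisation, and section 7.2 adds: "Patients will be randomized unblinded to one of the 3 groups".

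Other places differ:

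- The Summary, under Study design, has one rule for everybody: "For enrolment into the study a liverbiopsy at time of enrolment is compulsory and is advisable at end of treatment (week 48").
- Table 1 lists "Liver biopsy (preceding 12 months") in the screening column (weeks -4 to 0). Its heading covers all three groups and it does not split the row by arm.
- Table 3 has the biopsy "Performed at start of the study and repeated after 48 weeks", again without a split, although section 3 rules out a week-48 biopsy for controls.
- Section 7.1.3 lists the histology activity index and Ishak fibrosis score among the baseline characteristics to be documented for all patients.
- The inclusion criteria in section 4.2 do not mention a biopsy.

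The biopsy also feeds one screening step. Footnote (c) to the assessment schedule says: "Patients with cirrhosis or marked fibrosis on liver biopsy or raised AFP need to have a liver imaging study during the screening period". Exclusion criterion 18 then says: "Patients with a lesion suspicious of hepatic malignancy on a screening imaging study will only be eligible if the likelihood of carcinoma is" at most 10% after evaluation.

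**The concern.** An entry condition that depends on the group can be applied only once the group is known. Allocation is open, so the patient decides about an invasive procedure knowing the arm. The same unwilling patient is lost from a Peg-IFN arm and kept in the control arm. If such patients are then left out of the analysis, the treated arms are the biopsy-willing part of those randomised and the control arm is everyone randomised. The groups may then differ in ways that stratifying by genotype A does not address.

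The contradictions add a practical problem. A site following the Summary would require a biopsy of controls and a site following section 3 would not, so the two would enrol different control patients.

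**Working it through.** **The plan's own figure.** Inputs from section 4.4: 20% HBsAg loss on treatment, 1% in controls, two-sided Fisher's exact test, alpha 0.05, 44 per group, stated power 81%. Exact enumeration over both binomial distributions gives 80.6%, which reproduces it. Dropout: 44 / (1 − 0.10) = 48.9, so 49; the plan uses 50. Neither figure is disputed.

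**Assumption.** The documents give no biopsy refusal rate. I take r = 5%, 10% and 20% of patients allocated to treatment as an illustration.

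**Case A: refusers are left out of the analysis.** If the rate among all patients allocated is p = 0.20 and refusers would have had rate q, the rate among those who remain is (p − r·q) / (1 − r), and the shift is r(p − q) / (1 − r).

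| r | q = 0 (extreme) | shift |
|---|---|---|
| 5% | 0.20 / 0.95 = 21.1% | +1.1 points |
| 10% | 0.20 / 0.90 = 22.2% | +2.2 points |
| 20% | 0.20 / 0.80 = 25.0% | +5.0 points |

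With r = 20% and q = 10%, the rate is (0.20 − 0.02) / 0.80 = 22.5%, a shift of +2.5 points. The shift is zero if q = p and negative if q exceeds p, and nothing in the documents says which applies. Selection on spontaneous loss alone moves a 1% rate to at most 0.01 / 0.80 = 1.25% at r = 20%.

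*Numbers evaluable*, if refusers are not made up by further recruitment (section 7.5 rules out replacement after withdrawal and does not mention refusers): 50 × (1 − r) × 0.90 = 42.75, 40.5 and 36.0. That is about 43, 40 and 36 per treated arm against 44 required. The control arm stays at 45. The shortfall does not by itself lower the power at the planned rates: exact power at 43, 40 and 36 against 45 controls is 87.6%, 89.9% and 85.2%. These exceed 80.6% because Fisher's test is discrete. With no losses among controls, 5 losses give p = 0.055 at 44 versus 44 but p = 0.025 at 43 versus 45. What falls is the precision of the treated-arm estimate.

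**Case B: refusers stay in their allocated arm, untreated, and are analysed.** Assuming they lose HBsAg at the control rate, the treated-arm rate is 0.20(1 − r) + 0.01r.

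| r | treated-arm rate | power, 50 vs 50 | power, 44 vs 44 |
|---|---|---|---|
| 0 | 20.0% | 87.1% | 80.6% |
| 5% | 19.1% | 83.9% | 76.6% |
| 10% | 18.1% | 80.2% | 72.0% |
| 20% | 16.2% | 70.8% | 61.3% |

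Here there is no selection bias, but the effect is diluted and power falls. That is the reason to settle willingness before randomisation and not rely on the analysis set alone.

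**Biopsy-triggered imaging.** Ultrasound and Fibroscan (Table 1) and alfa-fetoprotein (Table 2) are marked at screening with no split by arm, and Table 3 also schedules ultrasound at screening or start. Raised AFP is a separate trigger in footnote (c). Controls therefore reach exclusion 18 as well; only the extra imaging prompted by histology falls mainly on the treated arms.

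**The case against.** The case on the other side has five parts.

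1. *The order of biopsy and randomisation is never stated.* Patients enter after eligibility is assessed, and Table 1 places the biopsy in the screening column. If the Summary governs, the difference between arms disappears. This stands as a limit on certainty: post-allocation loss is inferred. But section 3 speaks of patients already placed in a group, and in a randomised trial that can only follow allocation.
2. *Exclusion 22 already bars patients unwilling to follow study requirements.* It could remove likely refusers before randomisation. This stands in part. It does not name the biopsy, and under section 3 the biopsy is not a requirement for a control. The 12-month label in Table 1 suggests that a recent biopsy may suffice, which would also reduce refusals.
3. *Removal from the analysis is not stated.* Section 7.4.1 does not list biopsy refusal as a reason for withdrawal, and analysis sets may be defined in an SAP that is not at hand. This stands. Their absence is no fault of the Protocol; Case A follows only if failing an enrolment condition means not being analysed.
4. *A reader might infer that the treated arms are cleared by histology and controls are not.* The documents do not support that. No criterion names a histological finding, exclusion 6 covers only Child-Pugh B–C, and section 7.1.3 records cirrhosis as a baseline characteristic. Exclusion 9 refers generally to evidence of other liver disease, which a biopsy might supply, but this too is a narrow route.
5. *Sparing untreated controls an invasive procedure is defensible.* Agreed, and the fix keeps it.

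**Conclusion.** As written, section 3 makes entry depend on the allocated arm in an open-label trial, and the Summary, section 7.1.3 and Tables 1 and 3 contradict it. At assumed refusal rates of 5–20%, leaving refusers out shifts the treated-arm rate by about 1 to 5 points if none of them would have lost HBsAg. The shift is smaller, absent or reversed otherwise.

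A reader might go further and conclude that randomisation no longer protects the primary comparison. The documents do not support that. Against a planned 20% versus 1%, selection of this size is unlikely to produce a false positive. What is exposed is the effect estimate, baseline comparability (including histology, which will be incomplete in controls) and the number evaluable per treated arm. The sizes rest on assumed refusal rates and, for the bias, on refusers being left out of the analysis. The point is worth correcting because the correction is cheap.

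**What to change.** - Before randomisation, require every patient to agree to a baseline biopsy if allocated to treatment, and put this in section 4.2 and the consent wording.
- Settle all eligibility criteria before randomisation on data collected in all arms, and state when the biopsy takes place relative to randomisation.
- State that refusing the biopsy after allocation, or what it shows, does not remove a randomised patient from the analysis in the allocated arm. This concerns the analysis only, not the patient's clinical management.
- Reconcile the Summary, section 3, section 7.1.3 and Tables 1 and 3, including whether baseline histology is expected of controls and the week-48 entry in Table 3.

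Cost: protocol and consent wording. No control biopsies are added. A few patients unwilling to accept a possible biopsy will decline before randomisation, which may slow recruitment slightly.

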## 4 STUDY POPULATION

### 4.1 Population (base)

Patients will be enrolled into the study after assessment of eligibility. Target population will consist of adult patients ( $\geq 18$  years) with chronic hepatitis B (HBsAg positivity  $\geq 6$  months), HBeAg negativity, HBV DNA  $< 20,000$  IU/ml and ALT  $< 5^*$  upper limit of normal.

### 4.2 Inclusion criteria

1. Male and female patients  $\geq 18$  and  $\leq 70$  years of age
2. Positive HBsAg for more than 6 months.
3. Negative for HBeAg for more than 6 months.
4. HBV DNA  $< 20,000$  IU/ml
5. Patients with chronic hepatitis B who are either naive to antiviral treatment, or have received either interferon (IFN) or nucleoside/nucleotide analogues in the past but are still positive for HBsAg.
6. Serum ALT  $\leq 5^*$  ULN as determined by two values taken  $\geq 14$  days apart during the six months before the first dose of study drug with at least one of the determinations obtained during the screening period.
7. Negative urine or serum pregnancy test (for women of childbearing potential) documented within the 24-hour period prior to the first dose of test drug.

### 4.3. Exclusion criteria

1. Patients co-infected with HCV, HIV or who have decompensated liver disease, hepatocellular carcinoma, significant cardiac disease, significant renal disease, seizure disorders or severe retinopathy.
2. Patients who have received nucleos(t)ide analogues for their chronic hepatitis B within 6 weeks before enrollment or have received Peg-IFN within 3 months before enrollment.
3. Patients must not have received any other systemic anti-viral, anti-neoplastic or immunomodulatory treatment (including supraphysiologic doses of steroids or radiation)  $\leq 3$  months prior to the first dose of study drug or the expectation that such treatment will be needed at any time during the study.
4. Positive test at screening for anti-HAV IgM, anti-HIV, HCV RNA. (Patients that have cleared the hepatitis C virus can be included in the study)

5. Patients who are expected to need systemic antiviral therapy other than that provided by the study at any time during their participation in the study are also excluded. Exception: patients who have had a limited ( $\leq 7$  day) course of acyclovir for herpetic lesions more than 1 month prior to the first administration of test drug are not excluded.
6. Evidence of decompensated liver disease (Child pugh B-C)
7. Serum total bilirubin  $>$  twice the upper limit of normal at screening
8. History or other evidence of bleeding from esophageal varices or other conditions consistent with decompensated liver disease.
9. History or other evidence of a medical condition associated with chronic liver disease other than HBV (e.g., hemochromatosis, autoimmune hepatitis, metabolic liver diseases including Wilson's disease and alfa1-antitrypsin deficiency, alcoholic liver disease, toxin exposures, thalassemia).
10. Women with ongoing pregnancy or who are breast feeding.
11. Neutrophil count  $< 1500$  cells/mm^3 or platelet count  $< 80,000$  cells/mm^3 at screening.
12. Hemoglobin  $< 7.1$  mmol/L ( $< 11.5$  g/dL) for females and  $< 7.8$  mmol/L ( $< 12.5$  g/dL) for men at screening.
13. Serum creatinine level  $> 1.5$  times the upper limit of normal at screening.
14. Unstable ongoing severe psychiatric disease, especially depression (stable patients can be included).
15. History of immunologically mediated disease (e.g., inflammatory bowel disease, idiopathic thrombocytopenic purpura, lupus erythematosus, autoimmune hemolytic anemia, scleroderma, severe psoriasis, rheumatoid arthritis).
16. History or other evidence of chronic pulmonary and cardiac disease associated with functional limitation. Severe cardiac disease (e.g., NYHA Functional Class III or IV, myocardial infarction within 6 months, ventricular tachyarrhythmias requiring ongoing treatment, unstable angina or other significant cardiovascular diseases).
17. History of a severe seizure disorder or current anticonvulsant use and clinically unstable disease.
18. Evidence of an active or suspected cancer or a history of malignancy where the risk of recurrence is  $\geq 20\%$  within 5 years. Patients with a lesion suspicious of hepatic malignancy on a screening imaging study will only be eligible if the likelihood of carcinoma is  $\leq 10\%$  following an appropriate evaluation.
19. Major organ transplantation. (patients with skin, cornea or bone transplantation are allowed to be included into the study)

20. Thyroid disease with thyroid function poorly controlled on prescribed medications. Patients with elevated thyroid stimulating hormone or T4 concentrations, with elevation of antibodies to thyroid peroxidase and any clinical manifestations of thyroid disease that are not stable on prescribed medication are excluded. Stable patients can be included.
21. History or other evidence of severe retinopathy (e.g. CMV retinitis, macula degeneration) or clinically relevant ophthalmological disorder due to diabetes mellitus or hypertension.
22. Inability or unwillingness to provide informed consent or abide by the requirements of the study.
23. History or other evidence of severe illness or any other conditions which would make the patient, in the opinion of the investigator, unsuitable for the study.
24. Patients with a value of alfa-fetoprotein >100 ng/mL are excluded, unless stability (less than 10% increase) has been documented over at least the previous 3 months.
25. Evidence of current hard drug(s) (i.e. cannabis products are allowed) and/or alcohol abuse (20g/day for women and 30g/day for men).
26. Patients included in another trial or having been given investigational drugs within 12 weeks prior to screening.

